#### Inference criteria

We will follow conventional guidelines for interpreting Bayes factors [92] and regard BFs between 0.33 and 3 as reflecting ambiguous evidence. Model fit of latent-variable models will be evaluated using the root mean square error of approximation (RMSEA) alongside its 90% confidence interval, the standardized root-mean-square residual (SRMR), and comparative fit index (CFI). We will follow conventional standards indicating good fit [93]: RMSEA < 0.06, SRMR < 0.08, and CFI > 0.95. In addition, the chi-square statistic (χ^2^) will be reported. Differences in model fit will be examined using chi-square difference tests (Δχ^2^) and by examining the differences in AIC and BIC.

#### Hypothesis 1 (training gains)

To investigate gains in the trained domains, we will model latent change from (1) pretest to posttest, (2) pretest to follow-up, and (3) posttest to follow-up. Specifically, we will use performance in the three training tasks (drawings, numbers, shapes) as manifest variables loading on a latent variable each at pretest and posttest (or follow-up). To assess whether training gains in the experimental conditions exceed mere test–retest effects, we will run these latent-difference score models for multiple groups simultaneously (e.g., comparing dual task training to active control training) and test whether latent change differs between each experimental condition and the active control condition. We will compare each experimental condition separately to the active control condition. For all three experimental conditions, we expect positive latent change scores significantly larger than those observed in the active control condition, indicating improvement from (1) pretest to posttest and (2) pretest to follow-up. If training effects are maintained after training, there should be no negative latent change from posttest to follow-up.

#### Hypotheses 2 and 3 (transfer gains)

To test for group differences in training-induced gains in the untrained near and far domains, we will run latent-difference score models for the transfer domains (e.g., using the three working memory measures to load on a latent working memory factor at each pretest and posttest, or follow-up) and test whether latent change differs between each experimental condition and the active control condition. Positive latent change in the experimental conditions significantly larger than that in the control condition indicates transfer gains. The absence of negative latent change from posttest to follow-up will indicate that transfer gains are maintained after training.

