**Fig. 1 Fig1:**
[figure not shown]
Simplified Illustration of the Diffusion Model and Its Main Parameters. *Note*. After stimulus encoding, information accumulation begins at the starting point *z* and proceeds with a mean drift rate *v* until either response option A or B is reached, followed by response execution. The observed RT is the sum of the decision time and the time required for non-decision processes (*Ter*) such as stimulus encoding and response execution

Decomposing task performance into theoretically meaningful diffusion model parameter estimates can provide valuable insights into the mechanisms of transfer across the lifespan. First, the diffusion model parameters reflect trait-like properties of cognitive processes that are temporally stable and task-general [24], yet they are sensitive to age-related differences [25] and manipulations of attentional control demands [26]. These properties render the diffusion model parameters ideally suitable for investigating associations between intervention-specific effects and individual differences. Furthermore, previous research has shown that individual differences in drift rate are associated with mental abilities such as fluid intelligence [10, 27], making it a prime candidate mechanism potentially underlying the transfer effects observed in previous processing speed training studies. In the present study, we will be able to directly test this hypothesis by distinguishing training-induced changes in drift rate from such in response caution and non-decision components and evaluate how change in these cognitive processes contribute to transfer effects.

This preregistered study will follow methodological best practices [28–30] by including an active control group to account for test–retest and placebo effects, using multiple tasks to assess abilities on the latent level, and testing a sample large enough to provide adequate statistical power. Furthermore, our conclusions will be based on Bayesian inference, allowing for gauging the strength of evidence for the presence as well as the absence of any hypothesized effects and relationships.

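### The maintenance rule counts an undetected posttest-to-follow-up decline as maintenance, and is not tied to the planned control-arm comparison or Bayes-factor ambiguity band

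*Protocol article*

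**What the plan says.** Under *Hypotheses 2 and 3 (transfer gains)* the protocol article gives a rule for concluding durability: "The absence of negative latent change from posttest to follow-up will indicate that transfer gains are maintained after training". Under *Hypothesis 1 (training gains)* the same idea appears as an expectation: "If training effects are maintained after training, there should be no negative latent change from posttest to follow-up".

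The surrounding text contains material that bears on the rule but is not connected to it:

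- *Hypothesis 1*: "we will model latent change from (1) pretest to posttest, (2) pretest to follow-up, and (3) posttest to follow-up". The multi-group models compare each experimental arm with active control, and the controlled gain is expected at both later time points, "indicating improvement from (1) pretest to posttest and (2) pretest to follow-up".
- *Hypotheses 2 and 3*: the three measures of a domain "load on a latent working memory factor at each pretest and posttest, or follow-up", and the models "test whether latent change differs between each experimental condition and the active control condition".
- Background, section on the diffusion model: conclusions will rest on Bayesian inference, "allowing for gauging the strength of evidence for the presence as well as the absence of any hypothesized effects and relationships".
- *Inference criteria*: Bayes factors between 0.33 and 3 count as ambiguous. Model fit is compared by chi-square difference tests, AIC and BIC.
- *Missing data and data treatment*: analyses beyond pretest require at least one posttest session and 70% of training sessions. Follow-up attendance is not required, and nothing is imputed.

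**The concern.** The rule has two outcomes, decline or maintenance, and no place for uninformative data. The gain criteria beside it are worded in terms of significance, so the natural reading of an absent decline is that no significant decline was found. On that reading, less information makes a maintenance claim easier. Follow-up may well be the thinnest time point, because the analysis set does not require it.

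The rule as worded also looks at change within an arm. Follow-up is the third sitting of the same measures. A retest gain shared by all arms could offset a real loss of the training-specific gain, and a decline shared with control could be misread as lost transfer. Only the between-arm contrast separates these.

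Whether changes last beyond the end of training is part of the second objective, so a substantive conclusion depends on this sentence.

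**Working it through.** **1. The plan's own figure.** *Sample size* gives N = 280 for 80% power at α = 0.05 and f = 0.10, for a condition effect on pretest-to-posttest change. With 4 groups, 2 time points and an assumed correlation ρ = 0.5 (not stated), the noncentrality is

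λ = f²·N·m/(1 − ρ) = 0.01 × 280 × 2 / 0.5 = 11.2.

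On 3 and 276 degrees of freedom this gives power 0.806, so the figure reproduces. It does not cover posttest-to-follow-up change or any conclusion of no loss.

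**2. Numbers per arm.** 408/4 = 102. The allowance of about 15 to 20% attrition gives 102 × 0.85 = 86.7 (87) and 102 × 0.80 = 81.6 (82).

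**3. How often a true within-arm loss goes undetected.** The article gives no expected loss. I assume standardized losses (in SD of change) of 0.1 to 0.3; *Sample size* itself describes transfer effects as tending to be small. The check is a one-sample noncentral t with noncentrality d√n, counting a rejection only in the direction of loss. Example, n = 82 and d = 0.2: 0.2 × √82 = 1.81 against a two-sided critical value of 1.99 gives power 0.432, so 57% of such losses are missed.

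| True loss (SD of change) | Test at 0.05 | n = 102 | n = 87 | n = 82 |
|---|---|---|---|---|
| 0.1 | two-sided | 83% | 85% | 86% |
| 0.2 | two-sided | 48% | 55% | 57% |
| 0.2 | one-sided | 36% | 42% | 44% |
| 0.3 | two-sided | 15% | 21% | 23% |

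**4. Masking.** Let g be a change from posttest to follow-up shared by all arms and L the loss of the training-specific gain. The within-arm change is g − L, which is not negative whenever g ≥ L. The experimental-minus-control change is (g − L) − g = −L, so the shared part cancels.

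**5. What a controlled criterion can deliver at this sample size.**

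- Power of a two-sample test (two-sided 0.05) for a 0.2 SD difference in change against control is 25% (n = 82) to 30% (n = 102).
- For a margin-based test against control at 80% power, one-sided 0.025 and zero true loss, the smallest usable margin is (1.960 + 0.842) × √(2/n): 0.39 SD at n = 102 and 0.44 SD at n = 82. A 90% interval inside ±0.3 SD would be achieved in only about 21–38% of trials even with zero true loss.
- A Bayes factor for the null above 3, taking as an example a two-sample test with a Cauchy prior of scale 0.707, is still reached in 47% (n = 82) or 44% (n = 102) of trials when the true between-arm loss is 0.2 SD. For prior scales 0.5 to 1 the range is 34–56%. At scale 0.3 and n = 82 the threshold cannot be reached at all. The prior therefore has to be fixed beforehand.

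**The case against.** The strongest reply is that the plan already holds the safeguards. *Hypothesis 1* lists posttest-to-follow-up among the modelled changes, then runs the models across groups against active control, and explicitly expects the pretest-to-follow-up gain to exceed control. *Hypotheses 2 and 3* also compare latent change with control, and by their wording allow follow-up as the second time point. A reader might infer from the maintenance sentence that the plan has no control-arm comparison at follow-up. The documents do not support that: the omission is in the rule, not in the plan.

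A reader might also infer that the authors treat non-significance as proof of durability. That goes too far. The article commits to Bayesian inference, names an ambiguous range, and uses BIC, which can favour a no-change model. What stands is that the maintenance sentence does not invoke any of this, while the neighbouring criteria speak of significance.

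It is also fair to say that the article specifies no test for this step, that a negative change is directional (hence the one-sided figures), and that the loss sizes are mine. The 25–30% power in step 5 belongs to a two-sample comparison and does not measure how the stated rule performs. Finally, Hypotheses 1–3 are about pre-post improvement, and none of those tests depends on this rule.

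These points limit the severity. They do not repair a sentence that states what will indicate maintenance and leaves no room for an ambiguous result.

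**Conclusion.** The point holds, with moderate severity. The rule for transfer, and the parallel expectation for training gains, allow maintenance to be concluded from an undetected decline. They are not linked to the control comparisons or the Bayes-factor band that the article itself provides.

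If an absent decline means no significant within-arm decline, an assumed 0.2 SD loss would pass as maintenance in 48–57% of trials two-sided or 36–44% one-sided. Over assumed losses of 0.1 to 0.3 SD, the two-sided range runs from 83–86% down to 15–23%. These figures rest on the assumed loss sizes, 82–102 participants per arm and observed-score tests; power in the latent-variable models may differ somewhat. The possible masking by retest gains is a structural point, and the documents give no size for it.

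**What to change.** Replace the maintenance sentences for both training and transfer with one rule. Claim maintenance only if:

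1. the pretest-to-follow-up latent change in the experimental arm exceeds that of the active control; and
2. the experimental-minus-control difference in posttest-to-follow-up latent change gives a Bayes factor for the null above 3, the plan's own threshold, under a prior fixed in advance.

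Report a Bayes factor between 0.33 and 3 as inconclusive.

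Both parts are needed. Part 2 alone is lenient towards small losses (step 5). Part 1 protects against a complete loss: if no advantage over control remains, a two-sided 0.05 test would pass it in the favourable direction only 2.5% of the time. A partial loss can still pass both. One criterion should be chosen for part 2; offering a Bayes factor or a margin as alternatives would leave a choice between very different standards.

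The modelling cost is low, since the three intervals and the multi-group comparisons are largely planned already. The added work is to specify the prior and how the Bayes factor is obtained from the latent-change models. The real cost is in the conclusions: maintenance claims will be fewer and inconclusive results common at this sample size. The article should say so. The change should be made before follow-up data are analysed.

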#### Hypothesis 4 (attentional control demands)

To test whether increasing attentional control demands lead to larger transfer effects, we will run the same models as above but compare each experimental condition to each other. We expect training groups with higher attentional control demands to show significantly higher latent change scores than those groups with lower attentional control demands (i.e., dual task > switching task > choice RT task).

#### Hypothesis 5 (underlying mechanism)

To test whether training-induced changes in drift rate predict near and far transfer, we will combine the latent-change models for training and transfer domains and use the latent change in the training domain as predictor of the latent change in the transfer domain. We will compare (1) each experimental condition separately to the active control condition, and (2) the experimental conditions to each other. We expect that training-induced changes in drift rate are most strongly related to the size of transfer effect relative to the active control conditions if acquired in a training context with relatively higher attentional control demands (i.e., dual task > switching task > choice RT task). If the multigroup models fail to converge, we will attempt modeling the relationships for each group separately and for all groups together.

## Discussion

With this study, we aim to identify the cognitive processes changed by training speed tasks with varying attentional control demands across the adult lifespan. The results of this study will yield theoretical and practical implications. At the theoretical level, knowledge about the mechanisms underlying the success of processing speed training interventions will substantially advance understanding of individual differences and plasticity of cognitive abilities. By shifting the focus from the heated yet stagnating debate of whether cognitive training “works” [94] toward the more fruitful question of why some interventions are more successful than others [3], this study will enable a more productive debate. The use of diffusion modeling, a computational approach, will lead to developing a more precise theory of the cognitive processes involved in and affected by processing speed training. Critically, this project will move the cognitive training literature forward by testing a mechanism of transfer that so far has been neglected: the improved rate of evidence accumulation.

At the practical level, this project answers the WHO’s call for the development of evidence-based interventions that are accessible to everyone [95]. Cognitive training interventions are easy to administer, highly affordable, and can be distributed quickly. However, the current lack of knowledge about how the more successful interventions work, and why others do not, yields the risk of opportunity costs outweighing the potential benefits. We hope that our findings will provide a pathway to the development of powerful and, importantly, reliably successful cognitive training interventions. By identifying the mechanisms of training success across the adult lifespan, the results of this study can critically inform how interventions can be tailored to be maximally effective in counteracting age-related declines for people of all ages.

There are also a few potential limitations of this study. As this is an elaborate study that requires participants to invest a substantial amount of their time, we anticipate some attrition during the study. The sample size we aim for allows for some attrition (~15 to 20%), but we cannot predict how many participants will ultimately drop out. Higher than expected study drop-out could thus become a shortcoming of our study. Furthermore, due to this study being conducted across multiple sites in three different languages, findings may diverge between the sites, possibly due to differences in drop-out rate, cultural differences, language differences or other unforeseeable differences between the three sites. By adhering to the common experimental protocols, using carefully translated task instructions and study materials checked by native speakers, and regular meetings between the research teams of the three sites, we aim to minimize any of these potential site differences. Yet, on balance, the multi-site character of this study is of great added value and will allow for further-reaching interpretations of the results, which is worth taking the risk of possible site differences.

Taken together, the results of this study can contribute to identifying the cognitive processes that underpin training-induced cognitive change across the adult lifespan. This study goes substantially beyond previous research by using diffusion modeling to estimate theoretically and psychologically meaningful information processing components involved in performing the training tasks. As yet, no study has tested which diffusion model parameters underlie the benefits of processing speed training across adulthood. Combining diffusion and latent-change modeling to predict transfer and investigate the impact of attentional control demands during training is a novel and innovative approach that may explain why selective training interventions appear to be successful, whereas most other approaches failed to yield meaningful cognitive benefits. A better understanding of how processing speed training affects these cognitive mechanisms across the adult lifespan will enable researchers to maximize the effectiveness of cognitive training during adulthood in producing broad transfer to psychologically meaningful everyday life outcomes.

## Data Availability

Experimental tasks and non-proprietary stimulus materials will be shared on www.tatool-web.com and the Open Science Framework (https://osf.io/umzes). The study team will have exclusive use of the data until the main research findings are published. Following publication of the data, the anonymized data that can be ethically shared will be shared on the Open Science Framework (https://osf.io/umzes). Demographic data that will potentially allow for re-identifying individuals will be stored separately with controlled access. For these data, the Principal Investigators ([name], [name], and [name]) will jointly review applications to access the data and make the decision on whether to supply research data to potential applicants. Data will then be released on a case-by-case basis.

## Abbreviations

RT: Reaction time
CFQ: Cognitive Failures Questionnaire
QAM: Questionnaire d’Auto-évaluation de la Mémoire
EPT: Everyday Problems Test
DASS-21: Depression, Anxiety and Stress Scale-21 Items
ADL-PI: Activities of daily living-prevention instrument
BFI: Big five inventory
Grit-S: Short Grit Scale
TIS: Theories of Intelligence Scale
EXSE: Exercise Self-Efficacy Scale
GSE: General Self-Efficacy Scale
MoCA: Montreal cognitive assessment
CRIUGM: Centre de Recherche de l’Institut Universitaire de Gériatrie de Montréal
RAPM: Raven’s advanced progressive matrices
AIC: Aikaike information criterion
BIC: Bayesian information criterion
RMSEA: Root mean square error of approximation
SRMR: Standardized root-mean-square residual
CFI: Comparative fit index
